## Statistical data analysis

### Exploratory data analysis

Summary about data collected. Categorical data will be presented in frequency tables and histograms. Continuous values will be summarized according the mean, standard deviation and confidence interval.

Representation of categorical data through bar plots and continuous data through boxplots or density plots.

In other way, it will allow evaluating data quality and detecting anomalies (blank data, outliers, etc).

### Homogeneity analysis

Although the selection criteria and study design tend to preserve the homogeneity of the study groups, it is important to ensure that there are no external population effects. Therefore, the control variables mentioned above will be compared in order to assess the comparability of the groups.

Categorical variables will be compared using a Chi-square test, and for quantitative variables, a t-Student test (assuming normality, if it is not possible to assume it, a Mann-Whitney test will be applied).

### Objectives assessment

Main objective

In order to compare the effect of IVF versus ICSI on the blastocyst ploidy state a Poisson regression will be performed, which is the most appropriate statistical modelling method to analyse count data.

Secondary objectives

To compare IVF versus ICSI outcomes in preimplantation development outcomes:

- To compare the maturation rate, a t-test will be used to detect differences in the average number of mature oocytes (a Wilcoxon test will be used if we cannot assume normal distribution of data). If we found differences, linear or Poisson regressions will be performed to evaluate them in a model taking into account rest of explanatory variables.
- To compare the fertilization rate, a t-test will be used to detect differences in the average number of zygotes with 2PN oocytes (a Wilcoxon test will be used if we cannot assume normal distribution of data). If we found differences, linear or Poisson regression will be performed to evaluate them in a model taking into account rest of explanatory variables.
- In order to compare embryo quality on D3 (measured using the Istanbul consensus), a multinomial logistic regression will be performed.
- Embryo quality D5
  - To compare the blastulation rate, a t-test will be used to detect differences in the average number of embryos reaching at least the BL1 stage (a Wilcoxon test will be used if we cannot assume normal distribution of data). If we found differences, linear or Poisson regressions will be performed to evaluate them in a model taking into account rest of explanatory variables.
  - In order to compare embryo quality on D5 (The expansion stage of the blastocyst and the quality of the ICM and TE will divide the embryos into 3 categories), a multinomial logistic regression will be performed.
- To compare the utilization rate, a t-test will be used to detect differences in the number of embryos that can be used for the patient (a Wilcoxon test will be used if we cannot assume normal distribution of data). If we found differences, linear or Poisson regressions will be performed to evaluate them in a model taking into account rest of explanatory variables.
- In order to evaluate morphokinetic parameters defined by time-lapse imaging starting from the time of syngamy and their effect on ploidy, biopsy day, embryo arrest and gender, first we will present a trend chart to describe the average development times of the embryos according to the treatment. Then, growth models (linear or exponential) will be performed for each embryo, to estimate a growth parameter that can be compared between IVF and ICSI treatments.

To compare IVF versus ICSI outcomes in mtDNA:

- A t-test will be used to detect differences in the Mitoscore value depending on the treatment (IVF or ICSI) if we can assume normality distribution for Mitoscore value (in other case, a Wilcoxon test will be performed). Moreover, linear regression models will be performed to analyse the treatment effect in the presence of the remaining covariates.

To compare IVF versus ICSI outcomes in cycle outcomes:

- We will build a contingency table, and then, a chi-squared test will be used in order to compare the pregnancy, biochemical pregnancy, and clinical pregnancy results between IVF versus ICSI treatments. If we found statistical differences, a logistic regression will be performed to evaluate this differences in a model taking into account rest of explanatory variables.
- To compare the implantation rate, a t-test will be used to detect differences in this rate (a Wilcoxon test will be used if we cannot assume normal distribution of data). If we found differences, linear or Poisson regressions will be performed to evaluate them in a model taking into account rest of explanatory variables.

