# Abstract

ICSI is commonly used in PGT cases to eliminate any risk of sperm DNA contamination. With the switch from cleavage stage biopsy to biopsy of the full (hatching) blastocyst, this potential risk of contamination can be neglected and could allow the use of conventional IVF in PGT cases. Especially in cases of non-male factor infertility, the use of conventional IVF can be applied as a more ‘natural’ insemination method.

A pilot study will be performed on sibling oocytes including patients with non-male factor infertility and requesting PGT-A (NGS platform). If at least 10 cumulus oocyte complexes (COCs) are obtained after oocyte retrieval, half of the oocytes will be subjected to ICSI and the other half to conventional IVF. Preimplantation development is followed by time lapse imaging and blastocysts (day 5-7) fulfilling the biopsy criteria will undergo trophectoderm biopsy to detect the ploidy state and the mtDNA copy number.

The main objective is to analyse if the use a more physiological insemination method (IVF) has a beneficial impact on the ploidy state of the blastocyst as compared to ICSI within the same patient. As the embryos will be cultured in a time lapse imaging system, annotations can be made and the differences in maturation rate, fertilization rate and embryo development between both insemination methods can be analysed as secondary outcome parameter. On top of this, the PGT-A outcome will also display the mtDNA copy number which can be compared between IVF and ICSI biopsied sibling blastocyst. Euploid blastocysts will be transferred in subsequent FET cycles and give an indication on the clinical outcome between IVF and ICSI.

Would this study enable us to undermine the dogma to perform ICSI for all PGT cycles?

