## Subject Inclusion/exclusion criteria

*Inclusion criteria*

- Sperm parameters
  - Sperm concentration before capacitation: >15*10^6^ per ml (WHO)
    - Total motility (PR+NP,%): >40 (WHO)
    - Progressive motility (PR,%):>32 (WHO)
  - Sperm concentration after capacitation: >0.6*10^6^ per ml (not WHO defined)
    - Progressive motility (PR,%):>65 (WHO)
- ≥10 COCs after oocyte retrieval
- BMI ≤30 kg/m^2^
- Female age 18 to ≤ 40 years
- All ovarian stimulation protocols
- Fresh ejaculates
- Presence or absence of sperm morphology data: as we do not have a diagnostic sperm analysis for all patients, the presence or absence of >4% normal morphology (WHO) will not be taken into account, even with known low (<4%) normal morphology
- Couples requesting PGT-A
- Arab population

*Exclusion criteria*

- If after denudation (ICSI) only 2 mature oocytes are obtained
- If all time lapse spaces are occupied
- If the volume to be added after IVF is insufficient to perform IVF on all needed oocytes
- Presence of >1 *10^6^ per ml round cells in the ejaculate
- If a couple’s previous cycle was included in the study

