## Intervention and Follow-up

Couples that are eligible for the study will be selected on the day of OPU based on all inclusion and exclusion criteria (as described under “D. Subject inclusion/exclusion criteria”) and will be asked to participate in the study by signing the IC. A randomization list will determine to which group the first half (or one extra in case an odd number is available) of the oocytes will be assigned. As to prevent selection bias, oocytes will be assigned to both groups under low magnification and different cumulus expansion stages will be evenly divided. Oocytes selected for ICSI will be denuded and injected on the day of OPU after which their pre-implantation development will be followed by time lapse imaging. IVF oocytes will be inseminated (individual or per two) overnight with 10.000 PR sperm cells in a G185 incubator (K systems) and denuded in the morning of day 1 after which they will be transferred to the time lapse imaging incubator. Blastocysts of sufficient quality (to determine this, morphokinetic parameters shall be measured) will be biopsied on day 5-7 after which the blastocysts are vitrified individually. PGT-A (NGS platform) is performed on all TE biopsy samples and the ploidy state and mtDNA score will be provided. All annotated time lapse imaging data will be gathered and combined with the pre-implantation data, PGT-A data (ploidy state and mtDNA copy number) and all general patient and cycle characteristics. Patients with euploid embryos available will receive a FET and implantation rates and (clinical) pregnancy outcomes will be recorded.

The follow-up of the patients does not deviate from a normal fertility trajectory.

Quantification of the determining variables:

The primary outcome variable is the ploidy state

Secondary outcome variables are the (i) embryo development defined by the number of COCs retrieved, maturation and fertilization rate, embryo development analysed on day 3 and day 5, total number of embryos used for the patient, day of biopsy and the morphokinetic parameters; (ii) mtDNA copy number and (iii) the clinical outcome.

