### explanatory variables (INDEPENDENT)

Principal exposure factor

- Intervention: IVF or ICSI

Patient and cycle characteristics

- Sperm parameters before and after capacitation:
  - Concentration
  - PR
- BMI (kg/m^2^)
- Female age at the moment of OPU (years)
- AMH
- Smoking habit
  - Not smoking: 0
  - Smoking: 1
- Race
- Hormones on the day of trigger
  - E_2_ (pg/ml)
  - P (ng/ml)
- Ovarian stimulation
  - Ovarian stimulation protocol
  - Total dose of gonadotrophins used (IU)
  - Duration of stimulation (days)
- Trigger
  - Type
  - Units (IU)
- Abstinence duration
- Indication for PGT-A testing
- Endometrial preparation for FET
- Primary or secondary infertility

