## Sample Size

Considering no study has been performed analyzing the ploidy state, mtDNA content and embryo morphokinetics by PGT-A on IVF/ICSI sibling embryos, we propose a pilot study including 30 couples to assess the feasibility of the study. Moreover, the pilot study will allow us to estimate statistical parameters which enables us to calculate a sample size in a future study in which an acceptable level of power can be established.

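### Secondary per-couple outcomes: the adjusted model is run only after a difference is found, and it is filled with about 20 couple-level covariates that cannot move the arm estimate, while the couple term is not named

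*Protocol*

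**What the plan says.** **Design.** The Abstract states that "half of the oocytes will be subjected to ICSI and the other half to conventional IVF". Under Intervention and Follow-up, the split is randomised within each couple: "A randomization list will determine to which group the first half (or one extra in case an odd number is available) of the oocytes" goes to a given method. The Sample Size section reads: "we propose a pilot study including 30 couples to assess the feasibility of the study". It adds that the pilot should supply the parameters for sizing a later study.

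**Gate and model content.** Under Objectives assessment, maturation, fertilization, blastulation and utilization are each compared as average numbers, by a t-test or a Wilcoxon test. Then: "If we found differences, linear or Poisson regressions will be performed to evaluate them in a model taking into account rest of explanatory variables". Implantation carries the same condition. For pregnancy, biochemical pregnancy and clinical pregnancy the text is: "If we found statistical differences, a logistic regression will be performed to evaluate this differences in a model taking into account rest of explanatory variables".

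**Not gated.** The Mitoscore regression with the remaining covariates is planned unconditionally. The primary Poisson model and the day 3 and day 5 multinomial models carry no condition either, and their covariates are not stated.

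**Covariates.** The list of explanatory variables contains 20 items besides the arm, counting sperm concentration and progressive motility before and after capacitation as four. Nineteen are settled at or before retrieval. The exception is endometrial preparation for the frozen transfer.

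**Homogeneity.** In Homogeneity analysis, "the control variables mentioned above will be compared in order to assess the comparability of the groups", using chi-square, Student t or Mann-Whitney tests.

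No analysis names the couple as a term, stratum or pairing factor.

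**The concern.** The design makes each couple its own control. Covariates such as age, BMI or AMH cannot differ between a couple's IVF and ICSI oocytes, so for one count per couple per arm there is nothing for them to adjust. What the comparison needs is a term for the couple, because the two counts from one couple are expected to be correlated.

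The Protocol has this reversed. It spends about 20 covariates, which stand in only partly for the couple, and omits the couple. It also makes the model depend on the result of a preceding test, so for these outcomes the model may never be run.

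At stake are the error bars on the secondary outcomes and the usefulness of the pilot's variance estimates for planning. The homogeneity table would also read as evidence of comparability when it contains none.

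**Working it through.** **Inputs from the Protocol.** 30 couples, each in both arms; 20 listed covariates, 19 fixed at retrieval. That is 30/20 = 1.5 couples per covariate before multi-category factors are expanded.

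**Assumptions (the Protocol gives no figures).** Two-sided 5% level; outcome SD set to 1; within-couple correlation r from 0.3 to 0.7; one row per couple per arm (60 rows), no offset, no missing rows; covariates unrelated to outcome. There is no planned precision or power to reproduce.

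**Step 1: homogeneity tests.** Entering the same 30 couple values in both arms gives p = 1.00 for the t, Mann-Whitney and uncorrected chi-square tests. The two groups are the same list.

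**Step 2: arm estimate.** A covariate duplicated across arms is uncorrelated with the arm indicator, so in linear regression the arm coefficient stays the difference in means. In a log-link Poisson model the covariate factor is common to a couple's two rows, so the fitted arm ratio stays total IVF count / total ICSI count. In 200 simulated data sets, adding 19 covariates changed the arm coefficient by at most 3e-14 (linear) and 3e-15 (Poisson), which is rounding error.

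**Step 3: standard error of the arm difference.** With 30 couples the between-couple and within-couple parts have 29 degrees of freedom each, with variances (1 + r) and (1 − r).

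- Unadjusted: √(2/30) = 0.258, whatever r is.
- With 20 covariates: 29 − 20 = 9 between-couple degrees of freedom remain, so residual variance = [9(1 + r) + 29(1 − r)]/38.
  - r = 0.3: (11.7 + 20.3)/38 = 0.842
  - r = 0.5: (13.5 + 14.5)/38 = 0.737
  - r = 0.7: (15.3 + 8.7)/38 = 0.632
  - SE = √(2 × variance/30)
- Conditioning on couple: √(2(1 − r)/30).

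| r | Unadjusted | 20 covariates | Couple term |
|---|---|---|---|
| 0.3 | 0.258 | 0.237 | 0.216 |
| 0.5 | 0.258 | 0.222 | 0.183 |
| 0.7 | 0.258 | 0.205 | 0.141 |

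Mean simulated standard errors agree: 0.257 unadjusted; 0.236, 0.220 and 0.203 with covariates; 0.214, 0.181 and 0.140 paired. With 19 covariates the closed form gives 0.239, 0.225 and 0.210.

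**Step 4: error rate.** At r = 0.5 the simulated type I error is about 0.5% for an unpaired comparison, 1 to 2% with 20 covariates, and 4 to 5% with the couple. The unpaired test and the covariate model are conservative.

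**Step 5: gate.** If the first test is unpaired, r = 0.5 and the true difference is 0.3 SD, it reaches p < 0.05 in about 13% of simulated pilots. In the other 87% or so the model is not run.

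**Step 6: consequence for planning.** Required couples scale with variance. Ignoring the couple overstates the number for a paired follow-on study by 1/(1 − r): 1.43, 2.00 and 3.33 at r = 0.3, 0.5 and 0.7. Using the covariate model's residual variance overstates it by 0.842/0.7 = 1.20, 0.737/0.5 = 1.47 and 0.632/0.3 = 2.11.

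**Step 7: where the argument stops.** For embryo-level outcomes, couples supply unequal numbers per arm. With an assumed mean of 1.5 to 3 embryos per couple per arm, the between-arm difference in a couple-level covariate has an SD of 0.21 to 0.15 covariate SDs, and exceeds 0.2 SD in 32% to 17% of simulated studies. Adjustment is not empty there.

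**The case against.** Several points on the other side stand.

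- **The gate is not universal.** A reader might infer that adjusted results exist only for outcomes that passed a test. The Mitoscore regression is unconditional, and the primary and multinomial models are not gated.
- **The covariates are not identical across arms for every outcome.** Endometrial preparation belongs to a transfer, and a couple may have transfers from one arm only. A reader might infer that adjustment can never remove confounding in this trial. The documents do not support that for embryo-level or transfer-level outcomes (Step 7).
- **The adjusted arm effect is not made unstable or exaggerated.** With 20 covariates and 30 couples that inference is tempting. For per-couple counts, however, the adjusted estimate equals the unadjusted one, which the first test reports whatever the gate does. The shortage of between-couple degrees of freedom harms the covariate coefficients, not the arm contrast.
- **Adjustment is not useless.** It moves the standard error part of the way towards the paired value.
- **The t-test is not said to be unpaired.** If it were paired, Steps 4 and 5 would not apply to the first test. The follow-up regression would then be the less precise analysis, since it still lacks the couple.
- **Context.** This is a feasibility pilot, the outcomes are secondary, and covariate selection could be refined in a statistical analysis plan. Yet the Protocol itself fixes the gate and the use of all remaining variables.

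Race as a covariate, when eligibility specifies "Arab population", adds little or nothing but changes no result.

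**Conclusion.** The point holds for maturation, fertilization, blastulation and utilization, and for the couple-level homogeneity tests. For those four outcomes the gated model returns the same arm estimate with a standard error that is too large for a sibling design: 0.24 to 0.20, against 0.21 to 0.14 with a couple term, at correlations of 0.3 to 0.7. The homogeneity tests carry no information for retrieval-level variables.

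For implantation and the pregnancy outcomes the gate is equally unsound, but covariates can differ between arms, so the claim that adjustment is empty does not extend to them.

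The unchanged estimate and p = 1 follow from the design. The sizes depend on the assumed correlation and on one row per couple per arm. If the correlation were near zero the loss of precision would be small, but the gate would still be unjustified. No confirmatory decision rests on these models; the plan is wrong as written and should be changed.

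**What to change.** 1. Remove the conditions on finding a difference. For every secondary outcome, prespecify one model that is run whatever any first test shows.
2. Put arm and couple in that model: a paired analysis for per-couple counts, or a random intercept or fixed stratum for couple in embryo-level and transfer-level models. Replace the use of all remaining variables with few or no named couple-level main effects.
3. Replace the between-arm homogeneity tests with one baseline column for all couples, plus the number of COCs assigned per arm.
4. For transfer outcomes, describe the transferred subset by arm, including endometrial preparation.

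The cost is a change of analysis wording. No extra data are needed, and there is less analysis to do than now.

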### SECONDARY outcome measures (Dependent)

PGT-A:

- mtDNA copy number (de los Santos et al., 2018):
  - Mitoscore value: represents the normalized mtDNA content in (an)euploid embryos and indicates the total mtDNA content in the sample

Pre-implantation development:

- Number of COCs retrieved
- Maturation rate: number of mature oocytes obtained in each arm
  - ICSI: defined on day 0 as the number of injected oocytes/number of COCs assigned to the ICSI group
  - IVF: defined on day 1 as the number of oocytes with an extruded PB/number of inseminated oocytes
- Fertilization rate: number of zygotes with 2PN/number of oocytes assigned to the group
- Embryo quality on day 3 defined by the Istanbul consensus (Alpha Scientists, 2011)
  - The number of blastomeres and their division pattern, fragmentation, presence of compaction, vacuoles, granulation and nuclei will divide the embryos into 3 categories: good, fair or poor
  - Cell number on day 3 for all fertilized oocytes
- Embryo quality on day 5 (Gardner and Schoolcraft,1999) defined by the Istanbul consensus (Alpha Scientists, 2011)
  - The blastulation rate: number of embryos reaching at least the BL1 stage/ number of oocytes assigned to that group: defined by a 1 (yes, the embryo is blastulating) or 0 (no, the embryo is not blastulating)
  - The expansion stage of the blastocyst and the quality of the ICM and TE will divide the embryos into 3 categories according to Istanbul consensus
- Utilization rate: number of embryos that can be used for the patient (=number of embryos that can be biopsied)/number of oocytes assigned to the group
- Day on which the biopsy is performed (day 5,6 or 7)
- Morphokinetic parameters defined by time lapse imaging starting from the time of syngamy/PN fading (Basile et al., 2014)
  - t2: the timing to two cells
  - t3: the timing to three cells
  - t4: the timing to four cells
  - t5: the timing to five cells
  - t8: the timing to eight cells
  - SC: starting to compact
  - M: the timing to morula
  - SB: starting to blastulate
  - B: reaching a BL3 according to Gardner and Schoolcraft, 1999
  - F: reaching a BL4 according to Gardner and Schoolcraft, 1999
  - cc2: t3-t2
  - s2: t4-t3
- Biopsy yes or no: indicating developmental competence or developmental arrest
- Blastocyst gender: male or female

Clinical cycle outcome:

- Pregnancy (yes or no) defined by a βhCG test of > 15IU

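### Four secondary rates are tested as counts, and no secondary analysis states pairing or a couple effect although every couple supplies both arms

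*Protocol*

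**What the plan says.** **Design.** The Abstract of the protocol states that "half of the oocytes will be subjected to ICSI and the other half to conventional IVF", so every couple contributes to both arms. Under Intervention and Follow-up, a randomization list decides to which group "the first half (or one extra in case an odd number is available) of the oocytes will be assigned".

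**Definitions.** Secondary Objectives and Study Variables define four developmental outcomes as proportions. One reads "Fertilization rate: number of zygotes with 2PN/number of oocytes assigned to the group". Blastulation and utilization use the same denominator. Maturation is a proportion of COCs assigned in the ICSI arm and of inseminated oocytes in the IVF arm.

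**Tests.** Objectives assessment compares each of the four as a number, by t-test or Wilcoxon test: "To compare the fertilization rate, a t-test will be used to detect differences in the average number of zygotes with 2PN oocytes" is typical. Linear or Poisson regression with the explanatory variables follows only if a difference is found. For embryo quality the plan says "In order to compare embryo quality on D3 (measured using the Istanbul consensus), a multinomial logistic regression will be performed", and likewise for day 5. For mtDNA it says "A t-test will be used to detect differences in the Mitoscore value depending on the treatment (IVF or ICSI", followed by linear regression with covariates. None of these mentions pairing, a couple term or clustering.

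**Purpose.** Under Sample Size, "we propose a pilot study including 30 couples to assess the feasibility of the study", and the estimates obtained are to be used to "calculate a sample size in a future study in which an acceptable level of power can be established".

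**The concern.** There are two separate issues.

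First, the quantity tested is not the quantity defined. With 11 COCs one arm receives 6 oocytes and the other 5 (6/5 = 1.20, or 20% more), so equal rates give unequal expected counts. The list of explanatory variables does not include the number of oocytes assigned and no offset is named, so the follow-up regressions do not restore the denominator.

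Second, the two arms of a couple share the woman's age, stimulation, oocyte yield and semen sample. An analysis that ignores this puts between-couple variation into the error term of a couple-level test. It also gives wrong standard errors in an embryo-level test if the IVF–ICSI difference varies between couples. At stake are the secondary conclusions, the adjusted models that run only after a positive first test, and the variance estimates meant to size the next study.

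**Working it through.** **No planned figure to reproduce.** The protocol gives no alpha, power, effect size, standard deviation or correlation; 30 couples is a feasibility number. Everything numerical below rests on assumptions.

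**Step 1: definition against test.**

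| Outcome | Defined as | Tested as |
|---|---|---|
| Maturation | proportion | mean number of mature oocytes |
| Fertilization | proportion | mean number of 2PN zygotes |
| Blastulation | proportion | mean number reaching BL1 |
| Utilization | proportion | number of usable embryos |
| Implantation | proportion | rate |

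The mismatch is in the text for four rates. Implantation is the exception.

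**Step 2: is pairing stated?** It is not. The Wilcoxon test could be the signed-rank test. Homogeneity analysis, however, compares the control variables between arms by chi-square, Student t or Mann-Whitney. Many of those variables (age, BMI, AMH, stimulation) are identical in both arms by design, so that comparison makes sense only for independent groups. This points to an unpaired reading of the outcome tests but does not prove it.

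**Step 3: analytic effect of pairing.** For n couples and within-couple correlation r, the standard error of the arm difference is SD × √(2(1−r)/n) when paired and SD × √(2/n) when unpaired. Take n = 30, a difference of 0.5 SD and two-sided alpha 0.05 (assumed).

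- Unpaired: 0.5 × √30 / √2 = 1.936; 1.936 − 1.960 = −0.024; power 49%.
- Paired: 1.936 / √(1−r) − 1.960 gives power 49%, 58%, 71% and 87% at r = 0, 0.2, 0.4 and 0.6.
- True type I error of the unpaired test, 2(1 − Φ(1.96/√(1−r))): 5.0%, 2.8%, 1.1% and 0.2%.

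**Step 4: simulation of fertilization.** From the protocol: 30 couples, at least 10 COCs, halves differing by at most one oocyte, the odd one allocated at random. Assumed: 2PN rate 65% v 75%, mean COCs 14 or 18, between-couple ICC of the 2PN rate 0.02 to 0.20; 5,000 runs per setting.

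| ICC | Mean COCs | Type I error, unpaired counts | Power, unpaired counts | Power, paired counts | Power, paired rates |
|---|---|---|---|---|---|
| 0.02 | 14 | 0.9% | 26.7% | 55.4% | 56.0% |
| 0.02 | 18 | 0.3% | 12.4% | 64.3% | 63.6% |
| 0.10 | 14 | 0.4% | 15.3% | 51.1% | 53.4% |
| 0.10 | 18 | 0.1% | 5.7% | 61.0% | 60.2% |
| 0.20 | 14 | 0.0% | 4.7% | 44.7% | 47.4% |
| 0.20 | 18 | 0.0% | 1.9% | 56.0% | 56.4% |

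A separate simulation, also with 30 couples and 65% v 75%, gave 0.1–2.6% type I error and 13–46% power for unpaired counts, against 53–68% power for paired rates. Taken together: type I error about 0–3%, and power about 2–46% against 47–68%. The last two columns show that counts in place of rates matter little once the test is paired.

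**Step 5: the future study.** If pairing is ignored, the variance of the arm difference is overstated by 1/(1−r). The simulated within-couple correlation of counts was 0.45 to 0.82, so the factor is 1/0.55 = 1.8 to 1/0.18 = 5.6. A future split-oocyte study sized on that variance would be too large by the same factor.

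**Step 6: Mitoscore at embryo level.** Assumed: about 2.5 biopsied blastocysts per arm per couple, unit total variance, ICC 0 to 0.5.

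- Same IVF–ICSI difference in every couple: the t-test that ignores couples holds about 5% type I error and has 85–86% power for 0.5 SD. An unweighted couple-level paired test has 68–92% and is the stronger only at ICC 0.5.
- Difference varying between couples (variance 0.3, mean zero): the t-test that ignores couples rejects 8–10% of the time; the couple-level paired test rejects 4.5–5.7%.

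**The case against.** The strongest reply is that independence is being read into silence. The outcome tests are nowhere called unpaired, the rank test is named Wilcoxon rather than Mann-Whitney, and the Abstract frames the main comparison as within the same patient. Whether a t-test is paired is often settled in a statistical analysis plan, which is not shown here. This stands in part: a reader might infer that the protocol treats all siblings as independent, and for the t-test and Wilcoxon test it supports only that pairing is unspecified. It does not remove the point, because the protocol names its tests outcome by outcome and its homogeneity tests are of the independent-groups kind.

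Other stronger readings also fail:

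- That the extra oocyte biases a comparison. The randomization list decides which group receives it.
- That all secondary rates are tested as counts. Implantation is not.
- That power is lost throughout. Step 6 does not show this for Mitoscore, and nothing was simulated for the multinomial models.
- That false findings for age, BMI or AMH will follow from the embryo-level models. No stated objective tests those covariates; they only adjust the treatment effect.
- That the pregnancy comparisons share the fault. That depends on transfers per couple, which the protocol does not give.

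Finally, an unpaired count test is conservative, so it would miss differences rather than invent them, and the pilot claims no power.

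**Conclusion.** The point holds in this form. Four secondary rates are tested as numbers that leave out their defined denominators, and none of the secondary analyses uses the sibling design explicitly. The serious consequence is conditional: if the count tests are run unpaired, they reject far too rarely under the null, lose much of their power, and supply an inflated variance for planning. With paired tests, the count–rate mismatch is mainly a failure to test the defined outcome. For embryo-level outcomes, the case for a couple effect is error control when the arm difference varies between couples.

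All magnitudes depend on the assumed 2PN rates, COC numbers, ICCs and blastocyst yield. The outcomes are secondary in a 30-couple feasibility pilot, so this should be fixed but is not critical. The pilot's stated role in sizing a later study is the main reason not to leave it.

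**What to change.** In Objectives assessment, state that each of the four rates is analysed on its defined denominator with the couple as the matching unit: a paired t-test or Wilcoxon signed-rank test on the within-couple difference in rate, or a binomial mixed model (events out of oocytes in the group, arm, couple random intercept). Report the standard deviation of the within-couple difference for future planning.

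For day 3 and day 5 quality, Mitoscore and the morphokinetic comparisons, add a couple effect through a mixed model, or use GEE or cluster-robust errors by couple. A random intercept alone does not cover an arm effect that differs between couples, so allow that effect to vary where it can be estimated.

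The cost is wording and slightly more analysis work, with no new data. With 30 couples, models with a varying arm effect may not converge, so name a simpler fallback in advance, such as cluster-robust errors or a couple-level paired test.
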